#### Investigator’ calibration

The two examiners ([name] and [name]) were trained and calibrated prior to the trial, in order to achieve maximum reproducibility in the measurements. The calibration exercise for both centers was conducted at UNG before the beginning of the study, as previously described [53]. This exercise will be repeated once a year. Briefly, the standard error of measurement for continuous periodontal clinical parameters (PD and CAL) is evaluated. For the other clinical variables, the average level of agreement between the examiners is determined and considered satisfactory when the value is higher than 90% (Kappa test).

### Microbiological monitoring (baseline, 3, 6, and 12 months)

#### Sample collection

Nine subgingival samples are being collected per volunteer, three in each of the following categories: shallow (PD ≤ 3 mm), moderate (PD = 4–6 mm), and deep (PD ≥ 7 mm). The selected sites are located on non-contiguous interproximal teeth, preferably distributed across the four quadrants and subset according to baseline PD. Teeth with open margins and overhangs, furcation lesions, extensive caries, and/or endo-periodontal lesions are not selected for sampling. After recording the clinical parameters, supragingival plaque is removed and the subgingival samples are collected with individual sterile mini-Gracey curettes #11–12, positioned at the most apical portion of the subgingival sulcus/pocket and with a single apical-coronal movement. The samples are immediately placed in separate Eppendorf tubes containing 150 ul of TE buffer solution (10 mM Tris-HCl, 1 mM EDTA, pH 7.6), and then 100 ul of 0.5 M NaOH is added to each tube and the samples are dispersed using a vortex mixer. The samples are being stored at − 20 °C. The tubes containing the samples are previously identified with the volunteer’s code, date, and site collected.

#### Processing of microbiological samples

Counts and proportion of 40 bacterial species will be determined in each sample, using the Checkerboard DNA–DNA hybridization technique [54, 55]. The microbiological analysis will be entirely performed at the Laboratory of Microbiology of UNG. Briefly, the suspensions containing the bacterial biofilm samples will be boiled for 10 min and neutralized using 0.8 ml of 5 M ammonium acetate, and the DNA is released in the solution. The released DNA will be then placed into the extended slots of a Minislot 30 apparatus (Immunetics, Cambridge, MA, USA) concentrated on a 15 × 15 cm positively charged nylon membrane (Boehringer Mannheim, Indianapolis, IN, USA) and fixed to the membrane by baking it at 120 °C for 20 min. Subsequently, the membrane will be placed in a Miniblotter 45 (Immunetics, Cambridge, MA, USA) with the lanes of DNA at 90^0^ to the lanes of the device. Digoxigenin-labeled whole genomic DNA probes for 40 bacterial species are hybridized in individual lanes of the Miniblotter 45. After hybridization, the membranes are washed in highly astringent solution and the DNA probes are detected using the antibody to digoxigenin conjugated with alkaline phosphatase and chemiluminescence detection. The last two lanes in each run contain standards at concentrations of 10^5^ and 10^6^ cells of each species. Signals will be evaluated visually by comparison with the standards for the test species on the same membrane by a calibrated examiner (k test = 93%). The sensitivity of this assay will be adjusted to allow detection of 10^4^ cells of a given species by adjusting the concentration of each DNA probe [54–56].

### Immunological monitoring (baseline and 12 months)

#### Serum and GCF sampling

Peripheral blood samples and GCF are being collected 1 week after clinical examination. Two non-contiguous diseased sites (i.e., PD and CAL > 5 mm, BoP and no furcation involvement) and two non-contiguous healthy sites (i.e., PD and CAL < 4 mm without BOP and/or gingival bleeding) are being randomly chosen per patient for GCF sampling (among the same sites selected for microbiological sampling). After removal of the supragingival biofilm, the selected sites are isolated with cotton rolls and gently dried with an air syringe to eliminate saliva. GCF is collected by inserting standard paper strips (Periopaper, Oraflow Inc., Smithtown, NY, USA) up to approximately 2 mm into the sulcus/pocket for 30 s. Strips visually contaminated with blood are discarded. The GCF volume is measured in a calibrated device (Periotron 8000, Proflow Inc., Amityville, NY, USA), and the readings are converted into an actual volume (microliter, μl) by reference to a standard curve. Strips from the four selected sites are immediately placed into separate microcentrifuge tubes and stored at − 80 °C for subsequent assays. Peripheral blood samples are into an appropriate tube (Serum BD Vacutainer Plus Plastic Serum Tubes, BD, Franklin Lakes, NJ). Fasted samples are obtained in the morning for all patients. Immediately after blood collection, the serum is separated from blood by centrifugation (10 min at 1300 rpm) and stored in aliquots at − 80 °C.

### Processing of serum and GCF samples

The tubes containing the samples will be vortexed for 15 s and centrifuged for 5 min at 1500×*g* in order to elute. Samples will be analyzed using a Multiplex Bead Immunoassay (MAGPIX® System, Merck Millipore, Billerica, MA, USA) by means of a multiplex fluorescent bead-based immunoassay for 17 cyto/chemokines (eotaxin, GCSF, GM-CSF, interferon (IFN)-γ, IL-1β, IL-2, IL-6, IL-7, IL-8, IL-10, IL-12, protein chemoattractant monocyte [MCP]-1, MIP-1α, and tumor necrosis factor [TNF]-α) using commercially available kits (Milliplex Human Cytokine/Chemokine, EMD Millipore, Billerica, MA, USA) and a plate reader (Luminex. 100TM, EMD Millipore, Billerica, MA, USA), in accordance with the manufacturer’s recommendations. The amount of protein in each sample will extrapolate from standards using an appropriate software (Beadview EMD Millipore, Billerica, MA, USA). The minimum detectable concentrations for eotaxin, G-CSF, GM-CSF, IFN-γ, IL-1β, IL-2, IL-6, IL-7, IL-8, IL-10, IL-12, MCP-1, MIP-1α, and TNF-α are as follows: 1.2 pg/ml, 0.5 pg/ml, 9.5 pg/ml, 0.1 pg/ml, 0.4 pg/ml, 0.3 pg/ml, 0.3 pg/ml, 1.8 pg/ml, 0.2 pg/ml, 0.3 pg/ml, 10.5 pg/ml, 0.9 pg/ml, 3.5 pg/ml, and 0.1 pg/ml, respectively. The results will be reported as total amount (pg/site/30 s) and concentrations of cyto/chemokines per volume of GCF (pg/μl) and serum (pg/ml).

### Primary and secondary outcome variables

The primary outcome variable is the difference among groups for the percentage of volunteers achieving the clinical endpoint for therapy (≤ 4 sites with PD ≥ 5 mm) at 1 year post-treatment [57].

Secondary outcome variables are as follows: difference between baseline and 12 months post-therapy for mean CAL gain and PD reduction (in the full mouth and in different PD categories), mean number and percentage of volunteers with 0, 1–2, or ≥ 3 sites with different thresholds of residual pockets (e.g., PD ≥ 6 and ≥ 7 mm) at 12 months post-therapy; mean number (and mean reductions) of different thresholds of residual pockets at all post-treatment time points; difference among groups for the percentage of volunteers achieving different thresholds of BOP (e.g., ≤ 10%, 20% and 30% of bleeding sites in the mouth) at 1 year post-treatment; differences in the occurrence of adverse events among therapeutic groups; and differences in the counts and proportions of 40 bacterial species in the biofilm samples at all post-treatment time points and in the levels of 17 chemokines in the GCF and peripheral blood samples at 1 year post-therapy.

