## Background

Scaling and root planing (SRP), the standard of care for treatment of periodontitis, leads to an overall improvement in clinical parameters, including reduction in probing depth (PD), percentage of sites with bleeding on probing (BOP), and gain in clinical attachment [1–3]. However, SRP does not lead to major and sustainable clinical improvements in all subjects and periodontal sites, especially in cases of severe periodontitis [1, 4–6]. This is probably because SRP alone is unable to produce a sufficiently deep change in the oral microbial ecology (rebiosis) in order to produce a new stable climax biofilm community compatible with periodontal health [1, 2, 6–9]. Therefore, adjunctive therapies, such as systemic antimicrobials [6, 10–19] and probiotics [20–24], have been proposed with the purpose of potentiating the effects of SRP.

Among all the systemic antibiotics tested to date in the treatment of periodontitis, the combination of metronidazole (MTZ) and amoxicillin (AMX) has been shown to offer the greatest clinical and microbiological benefits. There is consistent scientific evidence showing that the adjunctive use of MTZ+AMX improves the outcomes of SRP, including a greater reduction in the number of deep pockets after treatment and, consequently, in the need for surgical interventions [19]. A number of ecological benefits have been associated with the use of MTZ+AMX during the active phase of treatment. This adjunctive therapy is effective in reducing key periodontal pathogens, such as *Porphyromonas gingivalis* and *Aggregatibacter actinomycetemcomitans* [25–30] in periodontal pockets and on other oral surfaces, and to foster an increase in the proportions of beneficial microorganisms [6].

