## Methods/design

### Aim, design, and setting of the study

The aim of this study is to evaluate the clinical, microbiological, and immunological effects of systemic probiotics as an adjunct to SRP alone or in combination with MTZ+AMX in the treatment of periodontitis. In order to address this aim, a double-blinded, four-armed, placebo-controlled, and bicentric RCT was designed. This study is being conducted at Guarulhos University (UNG; Guarulhos, SP, Brazil) and Federal University of Parana (UFPR; Curitiba, PR, Brazil). The study protocol was developed according to the Standard Protocol Items: Recommendations for Interventional Studies (SPIRIT) guidelines and using the SPIRIT checklist (Additional file 1) [49] and was registered in the ClinicalTrials.gov (NCT03733379) database.

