### Sample size calculation

The ideal sample size to assure adequate power for this study was based on the percentage of volunteers achieving “≤ 4 sites with PD ≥ 5 mm” at 1 year post-treatment [57]. Considering a difference of 44 percentage points between groups for volunteers achieving this clinical endpoint at 1 year post-treatment [5] and a significance level of 5%, 17 subjects per group would be necessary to provide a power of 80%. Considering an attrition of 25%, it was established that at least 22 subjects should be included in each treatment group. Considering a difference of 30 percentage points between groups for volunteers achieving this clinical endpoint at 1-year post-treatment and a significance level of 5% 37 subjects per group would be necessary to provide a power of 80%. Considering an attrition rate of 15%, it was established that 44 volunteers should be included in each treatment group (total 176 subjects).

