### Statistical analysis

#### Clinical monitoring

The chi-square test will be used to compare the differences in the frequency of gender and to compare the differences in the frequency of subjects achieving the clinical endpoint for treatment (≤ 4 sites with PD ≥ 5 mm) at 1-year (primary outcome variable) and of self-perceived adverse effects. Each individual continue/categorical variable will be computed per subject and then across subjects in each group. The significance of clinical differences over the course of the study will be sought using repeated measures ANOVA or Friedman multiple comparison tests (and their respective post-hoc tests, when necessary), and at each time point (among groups), using either ANOVA or Kruskal-Wallis multiple comparison tests (and their respective post-hoc tests when necessary) or ANCOVA with adjustments for the baseline values. Parametric or non-parametric tests will be chosen based on the normality of the data. A stepwise forward logistic regression analysis will be performed to investigate the impact of predictor variables on the clinical endpoint for treatment, i.e., “presence of ≤ 4 sites with PD ≥ 5 mm at 1-year post-therapy (yes/no).” The Number Needed to Treat (NNT) with each treatment protocol in order to obtain treatment success (≤ 4 sites with PD ≥ 5 mm) will be calculated using the following formula: NNT = 1/ARR, where ARR = |CER − EER| and CER = control group event rate and EER = experimental group event rate (http://ktclearinghouse.ca/cebm/glossary/nnt). The level of significance will be set at 5%. The data will be evaluated using intention-to-treat analysis with last observation carried forward.

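### The primary test looks for any difference among four arms, so a significant result would not identify the probiotic effect that the trial aims to study

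*Protocol article*

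**What the plan says.** - **Aim** (Aim, design, and setting of the study): to "evaluate the clinical, microbiological, and immunological effects of systemic probiotics as an adjunct to SRP alone or in combination with MTZ+AMX". This asks two questions about probiotics, one without and one with the antibiotics metronidazole plus amoxicillin (MTZ+AMX).
- **Arms** (Interventions): (i) SRP with both placebos, (ii) SRP with probiotic, (iii) SRP with MTZ+AMX, (iv) SRP with both. This is a complete 2×2 layout.
- **Prior belief about the antibiotics** (Background): "There is consistent scientific evidence showing that the adjunctive use of MTZ+AMX improves the outcomes of SRP".
- **Primary outcome** (Primary and secondary outcome variables): "The primary outcome variable is the difference among groups for the percentage of volunteers achieving the clinical endpoint for therapy", at 1 year.
- **Primary test** (Statistical analysis, Clinical monitoring): the chi-square test, used "to compare the differences in the frequency of subjects achieving the clinical endpoint for treatment". No pair of arms and no factorial contrast is named. The post-hoc tests in that section belong to the ANOVA, Friedman and Kruskal-Wallis analyses.
- **Sample size** (Sample size calculation): "Considering a difference of 30 percentage points between groups", giving 37 per group, or 44 per group after attrition. It does not say which groups are meant.

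**The concern.** The question is about probiotics, but the stated primary hypothesis has no direction and covers all four arms. Two of those arms contain a treatment that the article expects to work. The hypothesis that all four rates are equal is therefore expected to be false whatever the probiotic does, and rejecting it does not tell the reader which factor was responsible.

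At stake is the confirmatory standing of any statement about probiotics. If the primary result is significant, the claim must rest on some further comparison that this article has not fixed. A comparison chosen once the four percentages are known carries much less weight than one named beforehand.

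**Working it through.** **Inputs from the article:** four arms; 37 evaluable and 44 enrolled per arm; 5% significance; 30 points in the final sample-size calculation. **Assumptions:** two-sided testing (sidedness is not stated), SRP success rates of 10–40% (no rates are given), effects additive on the risk scale, and 30 points taken as the antibiotic effect for illustration.

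**1. The article's own sample size.** The two-group formula is

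n = [1.96·√(2p̄(1−p̄)) + 0.842·√(p₁(1−p₁) + p₂(1−p₂))]² / d².

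With d = 0.30 and p₁ = 0.20, p̄ = 0.35 and n = (1.322 + 0.539)² / 0.09 = 38.5, so 39. With p₁ = 0.15, n = 36. Lower rates from 5% to 65% give 27–43. The stated 37 therefore fits a two-group comparison with a lower rate near 15–20% (or 50–55%). For attrition, 37 / 0.85 = 43.5, so 44 per arm and 4 × 44 = 176, as stated. The calculation is for two groups, and the two groups are not named.

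**2. The four-group chi-square when probiotics do nothing.** Let arms i and ii have rate p, and arms iii and iv rate p + 0.30. Each arm lies 0.15 from the mean p̄ = p + 0.15, so Σ(pᵢ − p̄)² = 4 × 0.0225 = 0.09. The noncentrality is λ = 37 × 0.09 / [p̄(1−p̄)] = 3.33 / [p̄(1−p̄)], with 3 degrees of freedom. The last two columns are simulated rejection rates.

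| SRP rate | p̄ | λ | Four-group test, noncentral χ² | Four-group test, simulated | Probiotic contrast stratified by antibiotic (Cochran-Mantel-Haenszel), simulated |
|---|---|---|---|---|---|
| 10% | 0.25 | 17.8 | 96% | 97% | 5% |
| 20% | 0.35 | 14.6 | 91% | 92% | 5% |
| 30% | 0.45 | 13.5 | 88% | 89% | 5% |
| 40% | 0.55 | 13.5 | 88% | 89% | 5% |

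At 44 per arm the four-group test rejects in 93–98% (noncentral χ²).

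**3. When probiotics do something** (37 per arm, SRP rates 20–30%).
- Antibiotics add 30 points and probiotics 10: the four-group test is significant in about 93–94% of trials, the stratified probiotic contrast in 24–26%. The four-group result is almost the same as in step 2, so it hardly separates no probiotic effect from a small one.
- Only probiotics work, by 20 points: the four-group test has 54–60% power, the stratified contrast 72–76%.

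**4. Does another planned analysis supply the contrast?**
- The logistic regression is forward stepwise and names no predictors, so it need not keep a probiotic term or an interaction.
- The number needed to treat (NNT) is 1/|CER − EER|, with the control group's event rate as CER. It is an estimate, not a test. For arm iv against control it combines both treatments and does not isolate iv − iii.

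**The case against.** The strongest reply is that the article never says four-group chi-square. It says chi-square, sizes the trial with a two-group calculation, and computes an NNT for each protocol against control, so pairwise tests may have been intended. That is fair: the omnibus test is an inference from a difference among groups, four arms and no named contrast. Under the pairwise reading, however, the article still does not say which of the six pairs decides the trial.

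A further reply is that a separate analysis plan may name the contrasts. It may, but the article itself fixes a primary hypothesis and a test that do not match its aim, which is more than an omitted detail.

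Three stronger readings are tempting and are not supported:
- *A significant primary result would say nothing about probiotics.* This is too strong. The four percentages have to be compared, and the NNT for the probiotic arm rests on exactly the ii − i difference. The supported statement is that the test does not identify a probiotic effect.
- *Follow-up pairwise tests would run at 5% without correction, with an inflated family-wise error.* The article is silent on multiplicity for the chi-square, and silence does not establish that there would be no correction. The inflation would also depend on whether the pairs are tested only after a significant omnibus result.
- *The 44-point difference is the antibiotic effect.* The article does not attribute it to antibiotics, and it belongs to the 17-per-group calculation, not to the one giving 37. The 30 points used above are not attributed to antibiotics either.

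**Conclusion.** The point holds in this form: the primary hypothesis and test, as written, do not identify the probiotic effect named in the aim, and no other analysis in the article supplies the missing test. With no probiotic effect and a 30-point antibiotic effect, the four-group test is significant in about 89–97% of trials at 37 per arm, where a probiotic contrast rejects in 5%. These percentages rest on the assumed SRP rates and antibiotic effect and on the omnibus reading. The direction is the same across the whole range of rates tried. If the pairwise reading is right, the percentages do not apply, and the defect is that the deciding comparisons are not named.

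**What to change.** In Primary and secondary outcome variables and in Clinical monitoring, before unblinding:

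1. Name two primary comparisons of the 1-year success percentage: probiotic + SRP against SRP (ii − i), and probiotic + MTZ+AMX + SRP against MTZ+AMX + SRP (iv − iii). State a multiplicity rule, such as Holm at two-sided 5%.
2. Report as supportive the probiotic effect stratified by antibiotic, and the probiotic × antibiotic interaction with its confidence interval.
3. Make the four-group chi-square secondary. Keep probiotic against antibiotic (ii against iii) as a secondary comparison, because the Background names it as a gap in the evidence.
4. State in Sample size calculation which comparison the 30 points refer to.

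**Cost.** Wording only, with no new participants or data. Holm takes some power from each contrast. At 37 per arm it falls from about 79% to 76% for 30 points (assumed rates 20→50% and 50→80%), and from 46–48% to 39–41% for 20 points (assumed 22→42% and 60→80%). The stratified effect has more power (about 76% in the same 20-point case), but it can be read as one effect only if the interaction is small, and the trial has little power to check that. This is why it is proposed as supportive and not as primary.

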### Sample size calculation

The ideal sample size to assure adequate power for this study was based on the percentage of volunteers achieving “≤ 4 sites with PD ≥ 5 mm” at 1 year post-treatment [57]. Considering a difference of 44 percentage points between groups for volunteers achieving this clinical endpoint at 1 year post-treatment [5] and a significance level of 5%, 17 subjects per group would be necessary to provide a power of 80%. Considering an attrition of 25%, it was established that at least 22 subjects should be included in each treatment group. Considering a difference of 30 percentage points between groups for volunteers achieving this clinical endpoint at 1-year post-treatment and a significance level of 5% 37 subjects per group would be necessary to provide a power of 80%. Considering an attrition rate of 15%, it was established that 44 volunteers should be included in each treatment group (total 176 subjects).

### Randomization

The study coordinator ([name]), who is not involved in the inclusion and treatment of patients, assigned the study participants to one of the four treatment groups by means of a computer-generated random sequence (Random Allocation Software, http://random-allocation-software.soft). Randomization was stratified by center using permuted blocks of 4, 8, and 12. The study coordinator also organizes the bottles with the antibiotics tablets in opaque plastic bags labeled with the volunteer’s number. In addition, one clinical investigator and the study coordinator sent the randomization list to the *BioGaia AB Company* (Stockholm, Sweden). The company made and packed the probiotic (and placebo) lozenges in boxes labeled with each volunteer’s number. The bags are handed directly to the volunteer by the study coordinator. This sequence of procedures assures allocation concealment.

### Data collection and management

Clinical data are entered directly onto electronic spreadsheets (Microsoft® Excel 2011®, version 14.4.8, Copyright© 1990, Microsoft, Santa Rosa, California, USA), at the time of clinical examination, by a single investigator in each center. Data quality will be validated by checking missing data, out-of-range values, and invalid responses. The analyses will be conducted using a statistical program developed by Sigmund Socransky (Forsyth, USA), as well as SAS and GraphPad Prism (version 7.0) software.

### Statistical analysis

#### Clinical monitoring

The chi-square test will be used to compare the differences in the frequency of gender and to compare the differences in the frequency of subjects achieving the clinical endpoint for treatment (≤ 4 sites with PD ≥ 5 mm) at 1-year (primary outcome variable) and of self-perceived adverse effects. Each individual continue/categorical variable will be computed per subject and then across subjects in each group. The significance of clinical differences over the course of the study will be sought using repeated measures ANOVA or Friedman multiple comparison tests (and their respective post-hoc tests, when necessary), and at each time point (among groups), using either ANOVA or Kruskal-Wallis multiple comparison tests (and their respective post-hoc tests when necessary) or ANCOVA with adjustments for the baseline values. Parametric or non-parametric tests will be chosen based on the normality of the data. A stepwise forward logistic regression analysis will be performed to investigate the impact of predictor variables on the clinical endpoint for treatment, i.e., “presence of ≤ 4 sites with PD ≥ 5 mm at 1-year post-therapy (yes/no).” The Number Needed to Treat (NNT) with each treatment protocol in order to obtain treatment success (≤ 4 sites with PD ≥ 5 mm) will be calculated using the following formula: NNT = 1/ARR, where ARR = |CER − EER| and CER = control group event rate and EER = experimental group event rate (http://ktclearinghouse.ca/cebm/glossary/nnt). The level of significance will be set at 5%. The data will be evaluated using intention-to-treat analysis with last observation carried forward.

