**Statistical analyses:**

The significance of differences in each group (over the course of the study) will be sought using repeated measures ANOVA or Friedman tests and among groups (at each time point) using either ANOVA/ANCOVA or Kruskal-Wallis tests, depending on normality of the data. The chi-square test will be used to compare differences in the frequency of subjects achieving the clinical endpoint for treatment (≤ 4 sites with PD ≥ 5 mm) at 1 year and of self-perceived adverse effects. A stepwise forward logistic regression analysis will be performed in order to investigate the impact of different predictor variables on the percentage of patients achieving the clinical endpoint for treatment. The Number Needed to Treat (NNT) with different treatment protocols will be also calculated. Statistical significance will be set at 5%.

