**Fig. 2 Fig2:**
[figure not shown]
Schedule of volunteers’ enrolment, interventions, and assessments according to the SPIRIT statement. AMX, amoxicillin; Mo, months; MTZ, metronidazole

The administration of all medications (probiotic and antibiotics) and placebos starts immediately after the first SRP session. Antibiotics (or placebos) are given TID for 14 days and include two tablets, one of MTZ and one of AMX. Antibiotics and placebos are being specially prepared for this study by the same pharmacy (*Gallen Pharmacy and Manipulation* Ltda, Maringá, PR, Brazil). All tablets have the same color and size and are stored in properly coded opaque plastic bottles, containing 22 capsules/lozenges. Volunteers, therapists, and examiners are blind to the interventions applied.

Probiotic (or placebo) are administered two times per day for 90 days and include one lozenge every 12 h after brushing and flossing. The second lozenge is administered just before going to sleep. The lozenges are slowly dissolved in the volunteer’s oral cavity. Probiotic and placebo are being prepared for this study by *BioGaia AB* (Stockholm, Sweden). Probiotic lozenges contain 2 different strains of *Lactobacillus reuteri*: *L. reuteri* DSM 17938 and *L. reuteri* ATCC (PTA 5289), each at a minimum amount of 1 × 10^8^ CFU per lozenge. Placebo probiotic lozenges are identical to the active lozenges in taste, texture, and shape, but they do not contain *L. reuteri*. All lozenges are kept refrigerated at a temperature below 25 °C until they are handed to the patient.

SRP is performed using Gracey curettes (conventional and mini-fives) 5/6, 7/8, 11/12, and 13/14 under local anesthesia, and the treatment is completed in four to six sessions of approximately 1 h, distributed over a period of 14 days. At the end of each session, the clinical coordinator of each center evaluates the effectiveness of SRP using the outcome “smoothness of the scaled roots.” All volunteers will receive clinical monitoring at baseline and at 3, 6, and 12 months post-therapies. In addition, all subjects will receive periodontal maintenance every 3 months post-treatment until the end of the study. These sessions include OHI and supragingival/subgingival biofilm/calculus removal, as necessary. If any participant shows periodontal attachment loss ≥ 2 mm in 3 or more sites during the maintenance phase, they will be excluded from the study and referred for periodontal re-treatment.

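### For the continuous secondary outcomes, observed normality chooses between means and ranks visit by visit, and no rule says when the baseline-adjusted analysis applies

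*Protocol article*

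**What the plan says.** The Clinical monitoring part of the Statistical analysis section sets the comparison of arms visit by visit ("and at each time point (among groups"). Three tests are then offered for that comparison: "using either ANOVA or Kruskal-Wallis multiple comparison tests (and their respective post-hoc tests when necessary) or ANCOVA with adjustments for the baseline values". The selection rule is one sentence: "Parametric or non-parametric tests will be chosen based on the normality of the data". The Microbiological and immunological monitoring part repeats both statements for the bacterial and cytokine data. The abstract groups the tests slightly differently, "using either ANOVA/ANCOVA or Kruskal-Wallis tests, depending on normality of the data".

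Tests over time are a separate item. The abstract describes them as within-arm: "The significance of differences in each group (over the course of the study) will be sought using repeated measures ANOVA or Friedman tests".

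The visits are given under Interventions: "All volunteers will receive clinical monitoring at baseline and at 3, 6, and 12 months post-therapies". Immunological samples are taken only at baseline and 12 months.

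The outcomes concerned are secondary. Some are changes from baseline, such as "difference between baseline and 12 months post-therapy for mean CAL gain and PD reduction". Others are follow-up quantities, such as residual pocket numbers, bacterial counts and cytokine levels. The Randomization section says allocation was stratified by centre, but none of the listed among-group tests includes centre.

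**The concern.** Three tests are open for the same outcome, and they do not answer the same question. ANOVA compares means, Kruskal-Wallis compares rank distributions, and ANCOVA compares means at a common baseline value. Two choices are left loose:

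- **Parametric or rank.** This follows the observed data. One outcome could be analysed on means at 3 months and on ranks at 12 months, and the results would not line up.
- **ANOVA or ANCOVA.** Normality cannot settle this, since both are parametric, and no other rule is given.

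Baseline severity usually predicts follow-up severity, so leaving it out, or using it only through subtraction, costs precision. The secondary outcomes carry most of the trial's clinical, microbiological and immunological aims, so that precision matters.

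**Working it through.** **Plan's own figure.** The article gives no sample size, power or variance for any continuous outcome, so there is nothing to reproduce on this point. Its 37 evaluable per group (37/0.85 = 43.5, so 44 recruited; 4 × 44 = 176) is for the binary primary outcome. It serves below only as a realistic arm size.

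**Assumption.** The within-arm correlation r between baseline and follow-up is not in the article. The range taken is r = 0.3, 0.5, 0.7.

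**ANCOVA against ANOVA on follow-up values.** Variance ratio 1 − r²:

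| r | 1 − r² | Patients ANOVA needs, 1/(1 − r²) | Power with ANCOVA if ANOVA has 80% |
|---|---|---|---|
| 0.3 | 0.91 | 1.10 times | 84% |
| 0.5 | 0.75 | 1.33 times | 90% |
| 0.7 | 0.51 | 1.96 times | 98% |

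The last column is Φ((1.96 + 0.84)/√(1 − r²) − 1.96), for a pairwise comparison at two-sided 5%.

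**ANCOVA against change scores.** With equal variances at baseline and follow-up the ratio is (1 − r²)/(2 − 2r) = (1 + r)/2:

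| r | (1 + r)/2 | Patients the change score needs |
|---|---|---|
| 0.3 | 0.65 | 1/0.65 = 1.54 times |
| 0.5 | 0.75 | 1/0.75 = 1.33 times |
| 0.7 | 0.85 | 1/0.85 = 1.18 times |

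This table, not the first, applies to CAL gain and PD reduction, and its penalty shrinks as r rises. If the baseline SD is k times the follow-up SD, the change score has variance 1 + k² − 2rk in units of the follow-up variance. This exceeds 1 − r² by (k − r)², so the direction does not depend on equal variances, though the size does.

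**Simulation.** Four arms of 37, 3,000 runs per setting, r = 0.5 and 0.7, normal and log-normal data. The pretest was Shapiro-Wilk at 5% on residuals from the arm means.

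*No true difference, nominal 5%:*
- Pretest choosing ANOVA or Kruskal-Wallis: 4.3 to 5.4%.
- Smaller p-value of ANOVA and Kruskal-Wallis: 5.6 to 6.9%.
- Smallest p-value of all three tests: 7.7 to 10.0%.

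*Assumed arm shifts of 0, 0.25, 0.5 and 0.5:*

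| Data | r | ANOVA | Kruskal-Wallis | ANCOVA |
|---|---|---|---|---|
| Normal | 0.5 | 0.54 | 0.50 | 0.66 |
| Normal | 0.7 | 0.52 | 0.50 | 0.84 |
| Log-normal | 0.5 | 0.93 | 0.99 | 0.98 |
| Log-normal | 0.7 | 0.93 | 0.99 | 1.00 |

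The log-normal rows use ANCOVA on the raw scale. There Kruskal-Wallis without baseline does about as well, so for skewed outcomes the scale has to be fixed along with the adjustment.

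**The case against.** Several stronger readings are tempting, and the article does not support them.

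- **That p-values lose their 5% level after a normality pretest.** Applied mechanically, the pretest stayed close to nominal. The inflated rates arise only if an analyst picks the smallest p-value, which the article does not propose. They show why an undefined choice is undesirable, not what will happen.
- **That normality decides all three tests.** It separates parametric from rank tests only. Listing ANOVA beside ANCOVA also has an innocent reason: a comparison at baseline cannot be adjusted for baseline.
- **That baseline is ignored throughout.** CAL gain, PD reduction and the reductions in pocket numbers are changes from baseline, and a rank test on a change still uses it. For these the loss is inefficiency, not omission.
- **That arms will be compared through within-arm significance.** Among-group tests are planned at every visit, and nothing says a treatment effect will be claimed because one arm improved significantly and another did not.

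It can also be said that normality criteria, transformations and covariance structures belong in a statistical analysis plan, which is not shown. That stands for such detail. It does not dispose of the point, because what the article fixes is itself a data-dependent rule with an unranked alternative. A plan naming one test per outcome would have to depart from it.

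**Conclusion.** The point holds for the continuous secondary outcomes. The stated rule lets the target of inference vary by outcome and visit, and leaves baseline adjustment optional without a criterion. The main consequence is lost precision: under the assumed correlations of 0.3 to 0.7, ANCOVA has 0.91 down to 0.51 of the variance of an unadjusted follow-up comparison. With equal variances at both times, it has 0.65 to 0.85 of the variance of a change-score comparison. The correlations and simulated effects are assumptions, and the ratios suppose a roughly linear baseline relation on the scale analysed.

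A reader might infer that the trial's main conclusion is at risk. It is not: "The primary outcome variable is the difference among groups for the percentage of volunteers achieving the clinical endpoint for therapy", a binary outcome compared by chi-square. This is an improvement worth making, not a flaw that invalidates the plan.

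**What to change.** Remove the normality switch for post-treatment comparisons between arms and name one analysis per continuous outcome, adjusted for baseline value and centre:

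- **Clinical and microbiological outcomes:** ANCOVA at 12 months, or a mixed model over 3, 6 and 12 months with arm, visit, arm-by-visit, baseline and centre. The 12-month arm contrast is the main estimate.
- **Immunological outcomes:** ANCOVA at 12 months, since there is only one post-treatment visit.
- **Skewed outcomes:** prespecify the scale. Examples are a log scale with a stated rule for values below the detection limit for bacterial and cytokine levels, and a count model for pocket numbers.
- **Rank tests:** keep them as sensitivity analyses.
- **Within-arm tests over time:** label them descriptive.

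The cost is revised wording and slightly more programming in SAS, which the article already names. No new patients or data are needed. The downsides are output less familiar to readers used to ANOVA and the need to settle the handling of non-detects in advance.
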